#### Evaluation

We will evaluate the success of our team’s dissemination efforts based on the number of website hits, number of inquiries received, and number of physicians/clinicians responses to advertisements. We will obtain feedback on what is needed to translate research findings into practice in their setting.

#### Dissemination strategy summary

The research product of this study is the use of noninvasive transspinal stimulation along with locomotor training for individuals with spinal cord injuries or other upper motoneuron lesions. It can be used to maximize the benefits of traditional rehabilitation, and due to its noninvasive approach, it can be implemented in different real-life clinical settings worldwide. Our primary end users are patients, family physicians, physical therapists, hospital administrators, and medical schools. We plan to involve users in our dissemination efforts by leaflets written in lay language, demonstration of the intervention, and workshops. We will use the Christopher and Dana Reeve Research Foundation, Spinal Cord Injury Research Board of the New York State Department of Health, United Spinal Association—New York Chapter in Queens, New York, to help us disseminate our research product. We will communicate the results via publications in peer-reviewed journals, broadcast media avenues, and personal contact as outlined above. Potential obstacles that we face in disseminating the research findings and product include the skills required to implement our intervention in clinical settings. We will mitigate these obstacles via demonstration and clinical workshops organized at both research sites. We plan to evaluate the dissemination plan based on the number of inquiries received from the public, physicians, and patients, and we will encourage feedback from patients and clinicians. Responsibilities of the above-described dissemination plan will be equally distributed among all research team members. Specifically, both PI’s will be responsible for dissemination to hospitals and local-national SCI associations/foundations and publication of results in ClinicalTrials.gov, while the development of leaflets, website maintenance, and Abilities Expo will each be organized by 2 research associates.

## Discussion

Physical rehabilitation after SCI offers benefits, but rehabilitation alone is not enough to fully engage the plasticity needed to repair the nervous system. In this clinical trial, we apply non-invasive transspinal electrical stimulation to prime the nervous system before each session of physical rehabilitation (locomotor training). We use comprehensive neurophysiological and clinical assessments to measure recovery of nerve transmission, muscle reflex coordination, standing, walking, and quality of life. Understanding how transspinal stimulation augments exercise-based plasticity from neurophysiological and clinical perspectives is extremely important for the development of targeted and tailored neuromodulation interventions for SCI. Thus, this clinical trial will greatly impact clinical practice. This is because in real-world clinical settings, noninvasive transspinal stimulation can be more easily and widely implemented than invasive epidural stimulation. Additionally, by applying multiple interventions to accelerate motor recovery, we are employing a treatment regimen that resembles a traditional clinical approach, while administering two noninvasive therapeutic modalities that may have the ability to synergistically restore standing, walking, and other essential clinical functions in SCI.

## Trial status

This is the first protocol of the clinical trial with Identifier NCT04807764. Recruitment started in March 2021 and will be completed in approximately April 2025. Protocol amendment number: 2.

## Data Availability

Both PIs have access to all trial datasets in digital and/or paper formats. Investigators who work in the project as clinical coordinators, fellows, and research volunteers have access to the data pertaining to data analysis for different avenues of publications, but their access to data ends when their appointment is ended. Data sharing is not applicable to this article as no datasets were generated or analyzed during the current study. Any material required to support the protocol can be supplied on request.

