### Strategies to improve adherence to interventions {11c}

To maintain intervention fidelity, we developed and provided to staff members intervention protocols that detail the procedures for conducting the thoracolumbar transspinal stimulation and the locomotor training. To assure the correct implementation of the protocols, we trained staff members to become familiar with the theory and scientific literature supporting the intervention and with the laboratory equipment. We assess the fidelity with which the locomotor training is implemented in terms of compliance with the protocol and adherence to the procedure by recording for every session a participant received, the adjustments of a) BWS, b) leg guidance force, c) treadmill speed and by monitoring continuously participants’ engagement and performance using real-time biofeedback. Additionally, records of the thoracolumbar transspinal stimulation delivered are kept by staff members for each participant. Date, duration, and intensity of stimulation are recorded for every session, while the TEP threshold is established and recorded on a weekly basis. The position of the cathodal stimulation electrode is marked at the first session and checked in every session to ensure that electrode configuration remains the same.

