## Assignment of interventions: blinding

### Who will be blinded {17a}

Participants will be blinded to group allocation. Participants allocated to the sham group will receive stimulation at motor threshold intensity for 1 min, followed by a gradual return to no stimulation to mimic the initial sensation of stimulation followed by the acclimation to cutaneous stimulation. The study personnel performing locomotor training, clinical assessments, and data analysis will be blinded to the group allocation. Because each participant’s study code is not linked to the group assignment, those who perform data analysis cannot recognize the study group of a participant.

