### Data management {19}

All participants are given a unique identifying number that is used on all clinical and experimental data for that participant. Clinical data in paper format are kept in a locked file cabinet, while clinical data entered directly from the source documents along with the experimental data are saved with a unique code in password-protected computers.

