### Confidentiality {27}

Participant confidentiality is strictly held in trust by all investigators and staff. The study protocol, documentation, data, and all other information generated are held in strict confidence. No information concerning the study or the data are released to any unauthorized third party without prior written approval of the sponsor. Participants are consented individually and participate one at a time, which limits the opportunity for others to become aware of the participant’s participation or responses. All individually identifiable data is protected and only accessible to research staff.

All participants are identified by a study code upon randomization without any identifiable information. The study code is used to save all data in digital forms and written documents, and when data are reported either in a conference or in a research article. Furthermore, signed consent forms and all documents that can identify a participant are kept separate from all forms related to experimental procedures like subject data sheets or post-study questionnaires.

Informed consent documents and medical records: Informed consent is taken in a private, quiet room, and the investigator obtaining informed consent explains procedures thoroughly while asking if the participant has questions at several times during the process. Informed consent documents and medical records are kept separately from all other study data in a locked cabinet at both performance sites. The key is stored in a locked room separate from any of the participants’ data. Only authorized personnel have access to these cabinets.

Email/phone screening information: Information collected during the email or phone screen including names and contact information are entered into a secure database or locked in file cabinets in one of the labs. Once the participant has consented, documents containing protected health information or personally identifiable information are always kept separately from study data linked to the participant’s study code.

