### Methods in analysis to handle protocol non-adherence and any statistical methods to handle missing data {20c}

Non-adherence to the protocol will be assessed from the intervention log entered by each investigator/clinical coordinator who administers the intervention at each study performance site. If more than 5% of the experimental data values are missing, values will be encoded as − 1 or − 9999, replaced with the mean/median value, encoded as another level of a categorical variable and predictive models that impute the missing data will be applied [95].

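### The reason given for analyst masking (a study code not linked to group) does not secure it: the same code covers all records, and roles that deliver treatment also have the analysis data

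*Protocol article*

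**What the plan says.** Who will be blinded {17a} sets the rule: "The study personnel performing locomotor training, clinical assessments, and data analysis will be blinded to the group allocation". It supports the analyst part with one argument, that because each participant's "study code is not linked to the group assignment, those who perform data analysis cannot recognize the study group of a participant".

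Other sections describe the code, the records and the access:

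- Data management {19}: "All participants are given a unique identifying number that is used on all clinical and experimental data for that participant".
- Confidentiality {27}: "The study code is used to save all data in digital forms and written documents".
- Strategies to improve adherence {11c}, on the stimulation records that staff keep for each participant: "Date, duration, and intensity of stimulation are recorded for every session".
- The non-adherence section {20c} will judge adherence from "the intervention log entered by each investigator/clinical coordinator who administers the intervention at each study performance site".
- Procedure for unblinding {17b}: staff who perform the stimulation are not blinded, nor is the biostatistician who performs the allocation. Data are unblinded once data analysis is finished and group comparisons are due.
- The coordinating center section {5d}: each principal investigator leads delivery of stimulation and training at one site, and one of them, with the research team, makes all neurophysiological recordings.
- Data Availability: both principal investigators have all datasets, and "clinical coordinators, fellows, and research volunteers have access to the data pertaining to data analysis". The sentence goes on to refer to publications and to access ending with the appointment.

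**The concern.** {17a} does not only promise masking. It says why analysts are unable to identify the group. That argument holds only if nothing filed under the code reveals the arm, and if nobody doing the measurement already knows it. The article's own rules on data and access put both conditions in doubt.

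What is at stake is the measurement of the primary outcomes. Since {17b} keeps the data blinded until data analysis is complete, the plan relies on masking while raw recordings are turned into values. Under Outcomes {12}, that step includes accepting reflexes by an M-wave window of 2 to 8% of Mmax, fitting a sigmoid to obtain MEPmax, choosing the conditioning-test interval to carry forward, and taking mid-stance and mid-swing values. If the arm can be known at that point, a report of blinded analysis would rest on a reason that the rest of the protocol does not bear out.

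**Working it through.** No arithmetic applies. The check is whether the sections, read together, support the inference in {17a}.

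**1. Does anything under the code reveal the arm?** {19} and {27} apply one identifier to all clinical and experimental data and to digital and written material, with no exception for treatment records. {11c} says stimulation records exist for each participant and hold date, duration and intensity for every session. The comparator section {6b} describes sham as one minute at motor threshold followed by a ramp down to nothing. The intervention description {11a} gives active stimulation as 30 minutes at 1.2 times the soleus evoked-potential threshold. If the record shows what was actually delivered, an entry separates sham from active. It does not separate active standing from active supine, because posture is not among the fields listed. Two links are inferred from wording and not stated outright: that the log carries the study code (from the scope of {27}), and that the intervention log of {20c} contains the stimulation record of {11c}.

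**2. Could someone with the analysis data already know the arm?**

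- Stimulating staff: unblinded under {17b}.
- Clinical coordinators: named in {20c} among those who administer the intervention and enter the log, and in Data Availability among those with the data for analysis.
- Principal investigators: both lead stimulation delivery under {5d} and have every dataset under Data Availability.

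A person who delivered the stimulation knows the participant's arm, including posture, without needing the log. If the recordings carry the same code, that person can connect code and arm.

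**3. Is there a safeguard elsewhere?** {17a}, {17b}, {19}, {27}, {20c} and Data Availability contain no second code for analysis files, no restriction on who opens the stimulation records, and no rule that those who stimulate do not measure. {20c} does not say who derives adherence or when.

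**4. Result.** Neither condition needed for the inference in {17a} is secured. The code hides the participant's identity. On the text as written it does not hide the arm.

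**The case against.** The strongest reply is that access is not performance. {17a} states the operative rule that analysts are blinded, whereas Data Availability is an access statement. It assigns no tasks, gives no timing and refers to publications, so some or all of the access may follow unblinding. A reader might infer that staff measure the recordings of participants they stimulated; no section says so. The intervention also includes gait training, whose staff are said to be blinded, so a coordinator who administers the intervention did not necessarily stimulate. These points stand, and they limit the finding to what the plan fails to secure.

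A second reply is that the log's link to the study code is inferred and that {27} is about de-identification. This is fair, but {27} says all data and makes no exception. A reader might also infer that the records expose all three arms. They do not: the posture comparison is not open by that route.

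Third, Outcomes {12} fixes much of the measurement by numeric rule, which narrows the room for judgement. Some discretion remains, in an amount the article does not allow one to judge.

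Fourth, separate identifiers and file permissions often sit in a full protocol or data-management plan, and their absence from an article is not an error. That would be decisive if the article were silent on the mechanism. It states one, and draws from it a conclusion that its other sections do not support.

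**Conclusion.** The concern holds in limited form. {17a} claims a masking property that its stated mechanism does not deliver, because one code covers all records and the roles that administer or lead treatment overlap with those holding the data for analysis. This rests on reading {27} as including the stimulation records, and on those records showing what was actually delivered. The overlap of roles does not depend on either assumption.

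No magnitude is claimed. It is tempting to assume a measurement drift toward the active arms and convert it into an inflated error rate, but the article gives no basis for any drift. Such a figure would also ignore the planned Bonferroni post hoc tests. Setting the drift against the planning effects of 0.71 to 0.87 would compare unlike quantities, since those are single-group before-after differences. The document supports an unprotected route to bias in the primary outcomes. It does not show that bias, or an actual breach of blinding, has occurred.

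**What to change.** 1. Before off-line measurement, have the already unblinded biostatistician re-code the recordings under a new identifier and hold the key. This can also be done for recordings already collected but not yet measured.
2. Keep stimulation logs closed to anyone measuring outcomes until the derived primary values are locked. Have the biostatistician derive adherence from the logs in the meantime, and say so in {20c}.
3. State that staff who stimulated a participant do not measure that participant's recordings, or measure them only from re-coded files.
4. Reconcile {17a}, {17b}, {27}, {20c} and Data Availability: replace the reason in {17a} with the re-coding procedure, and give the timing and conditions of data access for coordinators and principal investigators.

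The cost is a small administrative burden of re-coding and file permissions. No visit, procedure or participant is added.

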## Abbreviations

AE: Adverse event
ANOVA: Analysis of variance
ANCOVA: Analysis of covariance
AIS: American Spinal Injury Association Impairment Scale
BP: Blood pressure
BWS: Body weight support
CPN: Common peroneal nerve
C-T: Conditioning-test
DSMB: Data and safety monitoring board
EMG: Electromyography
HR: Heart rate
H-reflex: Hoffmann reflex
IRB: Institutional Review Board
ISNCSCI: International Standards for Neurological Classification of Spinal Cord Injury
JJPVAMC: James J. Peters Veterans Affairs Medical Research Center
MEP: Motor evoked potential
Mmax: Maximal M-wave
NCMRR: National Center for Medical Rehabilitation Research
NICHD: National Institute of Child Health and Human Development
NIH: National Institutes of Health
NSCISC: National Spinal Cord Injury Statistical Center
OHRP: Office for Human Research Protections
PI: Principal investigator
SAE: Serious adverse event
SCI: Spinal cord injury
SUAE: Serious unexpected adverse event
TA: Tibialis anterior
TEP: Transspinal evoked potential
TMS: Transcortical magnetic stimulation
UAE: Unanticipated adverse event
UP: Unanticipated problem
